##### Electroacupuncture (EA)

Needles (0.30 mm in diameter, 40 mm in length, Hwato Brand, Suzhou Medical Appliance Factory, China) will be inserted vertically into the acupoints through the adhesive pads to a depth of 25–30 mm (Fig. 3). Acupuncturists will twist to achieve and enhance the sensation of needles inserted into the skin around acupoints, such as numbness, heaviness, aches, etc. (known as *De Qi*). Subsequent electrical stimulation (SDZ-V electroacupuncture apparatus, Huatuo brand, Suzhou Medical Appliance Factory, China) will be connected to each needle handle (a connecting wire connects a pair of acupoints, GB34 to ST32 and ST36 to SP9) and a continuous wave of 2 Hz frequency and an intensity of 1 mA will be maintained.

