### Outcome measures

#### Primary outcome measurement

The main evaluation criterion is pain, which is divided into two parts.

The first part is a visual analogue scale (VAS). The assessment schedule is shown in Table 1. Independent assessors who are not involved in acupuncture treatments will perform the VAS assessments (asking subjects to indicate the intensity of pain at the most painful points while resting and walking). The 0–100 mm VAS is used to evaluate pain intensity, wherein 0 mm denotes painless and 100 mm represents the most intolerable pain [32]. It allows patients to mark their own feelings on the scale as the evaluation score of pain. In addition to evaluating resting pain at 6 h after the operation, the pain in both the resting and active state is measured immediately after treatment on the first to third days after the operation, and assessed at follow-up on the fifth, seventh, and tenth days after the operation.

**Table 1 Tab1:** Schedule of trial enrollment, interventions, and assessments

Items	Enrollment (pre-operative)	Allocation (baseline)	Treatment (post-operative)				Follow-up		
Time point (hour/day)	-1	-1	6 h	1d	2d	3d	5d	7d	10d
Treatment sessions (n)	–	–		1	2	3			
Informed consent	√								
Assessment of eligibility	√								
VAS (resting)		√	√	√	√	√	√	√	√
VAS (active)		√		√	√	√	√	√	√
Additional dose released by PCA pump					√				
HSS score		√				√			√
HAMA score		√				√			√
AROM		√				√	√	√	√
PROM		√				√	√	√	√
COK				√		√	√	√	√
Discomfort and acceptance of EA				√	√	√			
Assessment of blinding method						√			
Postoperative complications and adverse events				√	√	√			

*VAS* Visual Analogue Score, *PCA* patient controlled analgesia, *HSS* hospital for special surgery, *HAMA* Hamilton Anxiety Scale, *COK* circumference of knee, *AROM* active range of motion, *PROM* passive range of motion

The second part is to record any additional doses from the patient-controlled analgesic pump after the operation, and to evaluate it uniformly on the second day after the operation (at 24 h after the first treatment).

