### EA safety and adverse events

Although acupuncture has been deemed a safe and reliable therapy, its adverse effects and complications associated should raise concerns [12]. Clinically, the incidence of minor adverse events related to acupuncture may be higher, such as pain, local infection, fatigue, local hematoma, subcutaneous hemorrhage, etc. [38, 39]. Some of these might be avoidable [40]. During the treatment period, acupuncturists will strictly abide by the operating rules of electroacupuncture [41]. All acupoints are around the knee joint(s). Acupuncture insertion is in the superficial or subcutaneous regions. Occasionally, there will be a small amount of bleeding or bruising. The bleeding can be arrested by pressing with sterile cotton swabs or cotton balls. The bruising usually disappears within 2–3 days [32].

In this study, during the entire clinical trial, observers who are also blinded to group allocation will record the adverse events (AEs) related to acupuncture treatment in detail and enumerate the incidences. AEs will be managed by acupuncturists and relevant clinical experts within 24 h. Any adverse event, whether related to treatment or not, is reported by the participants and practitioners at every visit.

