## Discussion

In recent years, with the development of fast-track (FT) surgery for joint problems, clinicians pursue the goals of painless, edema-free, stasis-free, and tubeless rehabilitation management after surgery [46]. For post-operative pain management, we should not only adopt the multi-mode analgesia model [47], but also promote the development of multi-disciplinary [48] approaches, especially by adding the high-quality analgesic methods of traditional medicine and developing the combination of traditional Chinese medicine and modern clinical medicine [49].

This clinical study of opposing needling on analgesia and rehabilitation after TKA is aimed at understanding the feasibility of such a procedure. Under the unified conditions of routine operation mode and routine intraoperative and post-operative analgesic dosage and on the premise of baseline equilibrium of the three groups, three interventions will be given according to each patient’s random number: opposing EA, operated side EA, sham EA.

Acupuncture on the affected side is a conventional non-drug therapy for rehabilitation after TKA [20, 50]. Opposing needling means applying acupuncture on the healthy leg (unoperated) of the patient, where acupoints are selected according to corresponding acupoints and meridian of the operated side. Accumulating evidence from clinical and experimental studies revealed that opposing needling exerts protective and facilitative effects on functional rehabilitation, the underlying mechanism of which remains to be further studied [51]. For patients, needling the healthy side after operation is more convenient and more acceptable. In terms of risk, needling the affected side increases the risk of infection after TKA. At the same time, the opposing needling method avoids the disadvantage of inconvenient selections of acupoints distributed at the surgical site.

In addition to the evaluation of the curative effect during hospitalization, good communication and follow-up with patients will be established. Not only will it help patients physically, but also care for patients psychologically. Through the study, we hope to provide clinicians with high-quality evidence of acupuncture for the recovery of pain and function after TKA and provide more ideas for clinicians in perioperative pain management.

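### Table 1 schedules adverse-event recording on days 1 to 3 only, while the safety text promises it at every visit and visits run to day 10

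*Protocol article*

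**What the plan says.** The protocol article gives two recording windows for safety data.

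- **Table 1 (Outcome measures).** The row "Postoperative complications and adverse events" carries ticks at 1d, 2d and 3d. The cells at 5d, 7d and 10d are empty.
- **EA safety and adverse events.** The text says that "during the entire clinical trial, observers who are also blinded to group allocation will record the adverse events (AEs) related to acupuncture treatment", and then: "Any adverse event, whether related to treatment or not, is reported by the participants and practitioners at every visit".

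Visits do not end with treatment. Under Primary outcome measurement, pain is also "assessed at follow-up on the fifth, seventh, and tenth days after the operation". Secondary outcome measurements places range of motion and knee circumference on the same three days.

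Infection has a particular role in this article. The Background says that concern about infection from needling near the incision led the team to consider opposing needling. The Discussion states as fact that "needling the affected side increases the risk of infection after TKA".

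**The concern.** A schedule of assessments is what site staff and form designers usually work from. If the case report form follows Table 1, no adverse-event entry is prompted after day 3, which is the day of the last needling. A complication that first shows itself later would enter the record only if someone remembered the safety text.

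This matters more here than in most small trials, for three reasons:

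- The Abstract names safety beside efficacy as an aim.
- Infection risk is part of the argument for opposing needling over operated-side needling, so the counts by arm are the only evidence on it that the trial itself can offer.
- Data management dispenses with a formal data monitoring committee, which puts more weight on routine event recording.

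**Working it through.** The article gives no adverse-event or infection rate, so there is no figure to reproduce. The check has two parts.

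**1. Reading the schedule.** Each row is aligned with the time-point header of Table 1. The six visit days from day 1 are:

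| Row | 1d | 2d | 3d | 5d | 7d | 10d |
|---|---|---|---|---|---|---|
| VAS, resting and active | yes | yes | yes | yes | yes | yes |
| AROM and PROM | – | – | yes | yes | yes | yes |
| COK | yes | – | yes | yes | yes | yes |
| Discomfort and acceptance of EA | yes | yes | yes | – | – | – |
| Complications and adverse events | yes | yes | yes | – | – | – |

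- Visit days required by the safety text (every visit): 6.
- Visit days scheduled in Table 1: 3.
- Shortfall: 6 − 3 = 3 visit days (5, 7 and 10), or half.

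The 6 h column is also blank. It is left out of the count because it precedes the first treatment. Other rows of the same table carry ticks through 10d, so the empty cells are not an effect of text extraction.

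**2. What a complete row would buy.** Inputs: 38 patients per arm (Sample size), two-sided α = 0.05, one pair of arms compared by Fisher's exact test. The infection rates are assumptions, since the article states none. Power is the sum, over all pairs of counts (a, b) with Fisher p < 0.05, of Bin(a; 38, p₁) × Bin(b; 38, p₂). The last column is the normal-approximation size for 80% power.

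| Assumed rates | Fisher power, 38 per arm | Needed per arm |
|---|---|---|
| 2% vs 4% | 0.2% | 1141 |
| 1% vs 5% | 0.8% | 285 |
| 2% vs 10% | 9% | 138 |
| 1% vs 10% | 13% | 100 |
| 1% vs 20% | 69% | 40 |

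Smallest significant split when one arm has no infection:

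- 0 vs 5 of 38: p = 2 × C(38,5)/C(76,5) = 2 × 501,942/18,474,840 = 0.054.
- 0 vs 6 of 38: p = 2 × C(38,6)/C(76,6) = 2 × 2,760,681/218,618,940 = 0.025.

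Six infections against none are therefore needed. With 0 of 38 observed, the one-sided 95% upper bound is 1 − 0.05^(1/38) = 7.6%. After the planned 15% dropout (38 × 0.85 ≈ 32 per arm) the bound is 1 − 0.05^(1/32) = 8.9%, and every power figure is lower.

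Extending the row to day 10 gives complete descriptive counts. It does not give a usable test of infection between arms.

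**The case against.** The strongest reply is that the safety text governs. It is explicit, nothing in the article says that the table overrides it, and staff who follow it would capture events to day 10. This stands, and it is why the loss is conditional. It does not remove the conflict, because the article gives no order of precedence either way.

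A second reply is that the row was meant for reactions to needling, like the row on discomfort, and so ends with treatment. The row's own title does not fit this: it covers postoperative complications, and the Background names infection and deep vein thrombosis among these after TKA.

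Four stronger readings are tempting, and the documents do not support them.

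- *That infection cannot be compared between arms because of the schedule.* Events on days 1 to 3 can be tabulated by arm even under the table, and events to day 10 if the text is followed. Infection is not a listed outcome, the article only promises to count incidences, and sample size is the tighter limit.
- *That patients go unobserved after the last needling.* Pain, range of motion and knee circumference are taken on days 5, 7 and 10. What is missing is a scheduled safety entry. For the same reason the gap is best counted in visits, since days 4, 6, 8 and 9 have no visit at all.
- *That the safety section contradicts itself on which events count.* Observers recording acupuncture-related events in detail, and participants and practitioners reporting any event, can be two compatible streams.
- *That the safety section's description of insertion as superficial or subcutaneous conflicts with the stated needle depth.* This has no bearing on the recording window. It also turns on tissue thickness, and on whether depth is counted from the pad or the skin; the article gives neither.

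**Conclusion.** The inconsistency is real and should be corrected. Table 1 schedules complication and adverse-event recording at 3 of the 6 visit days from day 1, and the safety section requires all of them. If the table is followed, events first seen on days 5, 7 or 10, infection included, may be missed, and the descriptive counts by arm would rest on days 1 to 3.

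The conclusion rests on the column alignment of Table 1, which is clear, and on the condition that staff work from the table. The size of any loss cannot be stated, because the article gives no event rates. The efficacy outcomes are not affected. The power figures rest on assumed rates and serve only to show that the corrected record should be read as description.

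**What to change.** In Table 1, tick the complications and adverse-events row at 5d, 7d and 10d so that it matches the section on EA safety. State that all adverse events, related or not, are tabulated by arm to day 10, as description and without a between-arm test.

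The cost is one extra case report form entry at each of three visits that already take place and already include measurements of the knee. No visit, patient or assessor is added.

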**Methods/design:**

This is a protocol for a randomized controlled patient- and assessor-blinded trial with three parallel arms (A, opposing EA; B, operated side EA; C, sham EA). *Yinlingquan* (SP9), *Yanglingquan* (GB34), *Futu* (ST32), and *Zusanli* (ST36) acupoints are selected for all three groups. In group A, the healthy side will be treated with EA, while the operated side will be administered sham EA. In group B, the operated side will be treated with EA while on the healthy side sham EA will be used. For group C, sham EA will be used on both sides. All patients in the three groups will receive treatment once a day for 3 days. The post-operative pain measured using a visual analogue scale score (including pain while resting and being active) and the additional dose of the patient-controlled analgesic pump after operation will be recorded as the primary outcomes. Secondary outcomes such as knee function and swelling, range of motion (including active and passive range of motion), post-operative anxiety, and acupuncture tolerance will also be assessed.

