**Fig. 1 Fig1:**
[figure not shown]
The flow diagram is intended to depict the passage of participants through this RCT

The study will be sequentially conducted as follows: 114 patients in Guanghua Hospital, Shanghai University of Traditional Chinese Medicine with osteoarthritis are included (surgical contraindications are excluded); after admission, unilateral TKA will be performed as scheduled. A day before the surgery, the eligible patients will be assessed at baseline and their consent will be obtained in writing. Patients will then be randomly assigned (on a 1:1:1 ratio) to the opposing EA group, the operated side EA group, or the sham EA group. Random numbers will be generated by the SPSS 22.0 software and sealed in opaque envelopes. Only the operator in charge of acupuncture treatment is authorized to open the envelope to obtain the group code.

The three groups of subjects will receive interventions on three consecutive days after surgery, once every day, by a clinician with more than 3 years of experience in acupuncture intervention. The participants will be blinded to the intervention measures. The success of the visit would be evaluated during the last visit of each participant. Researchers who did not participate in the treatment and who did not know the allocation results will perform the outcome assessment. Unblinding before the completion of the study will only be allowed in the case of medical emergencies or severe adverse events (SAEs).

All patients will receive the same post-operative analgesic dose with a fentanyl patient-controlled analgesic (PCA) pump (continuous infusion rate 0.25 μg/(kg·h)). Additional analgesics will be provided as per each patient’s requirements ascertained by the visual analogue scale (VAS) score > 6, and the use of analgesics will be recorded in their case report form (CRF).

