**Fig. 2 Fig2:**
[figure not shown]
Acupoints of treatment, EA, and sham EA

Patients will stay in a relaxed and supine position before the onset of treatment. The acupuncturist will untie the elastic bandage that was fixed during the operation, so that the acupoints are exposed. The skin around the acupoints is sterilized with cotton dipped in 75% alcohol, and a sterile adhesive pad (10 mm in diameter, 5 mm thick) is pasted on each of the acupoints (Fig. 3). The sterile adhesive pad is made of a special sponge (Suzhou Medical Appliance Factory, China) with one sticky side which can be pasted on the skin. The role of the sterile rubber pad is to fix the location of acupoints and to ensure subject blinding. The participants in the three groups will receive a 30-min treatment on the first, second, and third day after operation by the same acupuncturist, three times per session. It will be difficult for them to ascertain which group they belong to.

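### The primary PCA outcome, as worded, includes an untreated interval of variable length before the first session, which costs precision but does not bias the comparison of arms

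*Protocol article*

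**What the plan says.** The abstract makes the pump outcome primary alongside VAS: "the additional dose of the patient-controlled analgesic pump after operation will be recorded as the primary outcomes". The section Primary outcome measurement defines it: "The second part is to record any additional doses from the patient-controlled analgesic pump after the operation". On timing, the same section plans "to evaluate it uniformly on the second day after the operation (at 24 h after the first treatment"). Table 1 ticks this item once, on day 2.

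Treatment starts on day 1. According to Treatment protocol, participants "will receive a 30-min treatment on the first, second, and third day after operation". Study design and Table 1 place consent, baseline assessment and allocation on the day before surgery.

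On background analgesia, Study design states: "All patients will receive the same post-operative analgesic dose with a fentanyl patient-controlled analgesic (PCA) pump". It then turns to further drugs: "Additional analgesics will be provided as per each patient’s requirements ascertained by the visual analogue scale (VAS) score > 6". As for documentation, the same section says that "the use of analgesics will be recorded in their case report form (CRF"). It names no drug or route for these additional analgesics, and no primary or secondary outcome mentions them.

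Statistical analysis describes repeated-measures ANOVA for the primary outcome, on pain. It mentions no adjustment for pump doses taken before treatment.

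**The concern.** The count starts at surgery and ends at a time fixed by the first session. Its length is therefore 24 h plus each patient's own gap between surgery and session 1. The evaluation time is uniform relative to treatment, but the length of exposure is not.

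Demand in the gap cannot respond to a treatment not yet given, so it enters the outcome as variation unrelated to the arms. With one scheduled reading, the analysis cannot separate the two periods. At stake is the ability of a primary outcome to detect a real reduction in pump use, and the size of the reduction that would be reported.

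A second, smaller matter is that a reader cannot tell whether the VAS-triggered additional analgesics in Study design are the same as the additional pump doses in Primary outcome measurement.

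**Working it through.** **Figures in the plan.** There is no plan figure to reproduce. The protocol gives no mean, SD or effect for pump doses and no hours from surgery to first session. Its sample size section uses VAS only. The figures below therefore rest on stated assumptions.

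**Inputs**

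- From the protocol: the count opens after the operation and closes 24 h after session 1; session 1 is on day 1; allocation is on the day before surgery.
- Assumed: a gap of P hours before session 1, mainly 12 to 24 h; a true 30% reduction after treatment starts; a constant untreated demand rate r per hour.

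**Share of the window before treatment** = P/(P + 24). For P = 12, 12/36 = 33%. For P = 24, 24/48 = 50%.

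**Relative effect**

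- Post-treatment 24 h only: 24r against 0.7 × 24r = 16.8r, a difference of 7.2r.
- Whole window, P = 12: 36r against 28.8r. The difference is still 7.2r, but 7.2/36 = 20%.
- Whole window, P = 24: 48r against 40.8r. The difference is 7.2r, and 7.2/48 = 15%.
- If the rate before treatment is twice the later one: 7.2/48 = 15% for P = 12 and 7.2/72 = 10% for P = 24.

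The expected absolute difference is unchanged. Only the percentage shrinks.

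**Power.** Set the SD of the post-treatment dose to 1 and let SD be proportional to hours, so the pre-treatment SD is s = P/24. With pre/post correlation ρ, the variance of the total is 1 + s² + 2ρs. Start from a comparison with 80% power (two-sided 5%) on the post-treatment window, so the standardised effect is 1.960 + 0.842 = 2.802. Power on the whole window is Φ(2.802/√variance − 1.960).

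- P = 12, ρ = 0: variance 1.25; 2.802/1.118 − 1.960 = 0.546; power 71%.
- P = 24, ρ = 0: variance 2.00; 2.802/1.414 − 1.960 = 0.021; power 51%.
- P = 12, ρ = 0.8: variance 2.05; 2.802/1.432 − 1.960 = −0.003; power 50%.
- P = 24, ρ = 0.8: variance 3.60; 2.802/1.897 − 1.960 = −0.483; power 31%.

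| Gap P | Pre-treatment share | True 30% shows as | Power, ρ = 0 | Power, ρ = 0.8 |
|---|---|---|---|---|
| 12 h | 33% | 20% | 71% | 50% |
| 18 h | 43% | 17% | 61% | 39% |
| 24 h | 50% | 15% | 51% | 31% |
| 30 h | 56% | 13% | 42% | 26% |

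The variance is also the factor by which the sample would have to grow to keep 80% power: 1.25 to 2.00 at ρ = 0, and 2.05 to 3.60 at ρ = 0.8, for 12 to 24 h. These figures hold P fixed within each row. Variation in the gap between patients would add further variance.

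**The case against.** The strongest reply is that an article condenses the full protocol, and the exact start of the count may be fixed elsewhere. Tying the evaluation to session 1 is also compatible with a count over the following 24 h only. That reading is possible, but the article does not merely omit the start. Both the abstract and the outcome section say that doses after the operation are counted, and Table 1 schedules no pre-session reading from which a 24 h count could be formed.

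It is also fair to say that the size is assumed throughout, and that the planned tests compare groups rather than estimate a percentage reduction. The loss of precision, however, affects any such test of the unadjusted total.

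Three stronger readings are tempting, and the documents do not support them:

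- **That the window biases or misranks the arms.** Patients are allocated the day before surgery, so demand before session 1 is balanced in expectation, and the expected absolute difference is unaffected.
- **That rescue given outside the pump is left out, so rescued patients look like low users.** Study design states no drug or route. The additional analgesics may be the additional pump doses themselves. Misranking would need non-pump rescue that exists, differs by arm and replaces pump doses, none of which is stated.
- **That reading at 24 h is wrong because it captures little beyond session 1.** That is a design choice. The VAS part covers all three sessions and follow-up to day 10.

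**Conclusion.** The point holds as one of precision. On the stated definition, the pump outcome mixes untreated hours of variable length with the 24 h after session 1, and no adjustment for the untreated part is described. With an assumed gap of 12 to 24 h, constant demand and SD proportional to hours, one third to one half of the window precedes treatment, a true 30% reduction shows as 20 to 15%, and 80% power falls to about 71 to 51% (correlation 0) or 50 to 31% (correlation 0.8). The direction follows from the wording, but the size cannot be fixed from the documents. The change is worth making because the outcome is primary and the remedy is small.

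On the additional analgesics, the finding is only that Study design and Primary outcome measurement must be reconciled. Neither an omission of analgesic use nor a bias from it is established.

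**What to change.** - Read the pump counter immediately before session 1 and again 24 h later, and add the first reading to Table 1. Define the outcome as the additional dose between the two readings.
- Include the pre-session dose as a covariate. Unadjusted, it is noise. As a linear covariate it leaves a residual variance of 1 − ρ² for the post-treatment dose, which is 1 − 0.64 = 0.36 at ρ = 0.8.
- State whether the CRF-recorded additional analgesics are the pump's additional doses. If they are the same, say so and count them once. If they are separate, combine their use over the same 24 h with the pump doses into one total additional analgesic measure, with the conversion to a common dose stated in advance. Adding them without settling this could count the same doses twice.

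The cost is one extra reading at a visit that already takes place, a revised outcome definition and, only if the analgesics are separate, a conversion rule in the SAP. Only measurement and analysis change; patient care does not.
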